### Intervention

#### Overview

The intervention is called Go for Fiber Against Risk of Diabetes (GO-FAR), which is a fully mHealth-adapted version of an existing intervention, Fiber for the Improvement of Behavior, Eating, and Risk (FIBER), which has been described elsewhere [8]. In brief, the intent of FIBER is to focus singularly on promoting greater intake of fiber via a combination of in-person group-based sessions as well as phone-based motivational interviewing and nutrition counseling, which span 3 months. GO-FAR is a fully remote mHealth adaptation that was created by mapping FIBER to its core behavior change techniques and then, ultimately, to an mHealth-compatible version [28]. In total, GO-FAR includes 3 core elements, each described below: fiber-focused messaging delivered in both video and text format up to twice per day for 3 months, biofeedback in the form of CGMs, and home-delivered high-fiber foods.

#### Intervention Messages

Video-based content was designed to target SDT and SCT constructs, including those targeted in FIBER [8]. Specifically, videos were designed to be short (<1 minute each) and cover areas such as what fiber is, where to find it, how to incorporate it into meals, how it affects blood glucose differently than other carbohydrates, how it differs in isolated or synthetic vs intrinsic forms, and how to cope with side effects that often occur (eg, digestive discomfort). Each video is delivered once per day in sequential order and after completion of the morning daily diary. Participants are encouraged to watch every video as videos build on one another in terms of content and complexity. For example, earlier videos cover basic information, such as what fiber is (a carbohydrate found in plant food). Later videos cover how fiber is different from other carbohydrates that cause increases in blood sugar, such as monosaccharides or refined starch.

In addition to the messaging videos, individual coping messages were designed based on existing evidence regarding factors that influence fiber intake, including GI responses, feeling short on time, and poor motivation for eating fiber [22]. These messages were designed using an acceptance and commitment therapy–informed approach, for example, increase in acceptance of short-term negative feelings or discomfort in pursuit of long-term goals [52]. These coping messages are delivered using a just-in-time adaptive intervention framework based on participants’ real-time EMA responses (described below). In brief, EMA responses related to key determinants of fiber intake (eg, GI discomfort, perceived time constraints, motivation, and cravings) are evaluated in real time using prespecified thresholds. When participants endorse a given factor at or above a defined threshold (eg, moderate or high levels), a corresponding coping message is delivered immediately following EMA completion and prior to video content delivery. If no factors exceed the defined thresholds, participants receive standard educational video content only. In cases in which multiple factors exceed thresholds, a prioritization schema is applied to ensure delivery of the most contextually relevant coping message. Message selection is deterministic and mapped to specific EMA responses, ensuring consistency in intervention delivery across participants.

All intervention components, including EMA prompts, coping messages, and video content, are delivered via the Insight platform and are time-stamped and logged. Engagement metrics will include EMA completion rates and intervention delivery records. These data will be used to assess intervention fidelity and participant exposure, which are critical for interpreting both feasibility and preliminary efficacy outcomes.

#### Biofeedback

Biofeedback in this study will be obtained via the use of CGMs. The CGM used will be the Dexcom G7. Participants will be given a G7 device at their baseline visit and walked through how to self-insert it with research personnel trained by the team of coauthor [name]. They will also be handed a second G7 device and instructed to self-insert it at the midpoint of the intervention (approximately 6 weeks). The CGM will not be used as a means of measuring glycemic control but, rather, will be used as a form of biofeedback to allow participants to observe the glycemic effects of adding high-fiber foods to their diet.

#### High-Fiber Foods

High-fiber foods will be delivered to participants’ homes once per week for 12 weeks. These foods are not intended to be the sole source of nutrition for participants but, rather, an additional behavior change technique (eg, adding objects to the environment) [28]. All foods have naturally occurring fiber, or intrinsic fiber. That is, they are not specialty products that have extra fiber added (isolated or synthetic), such as specialty breads, tortillas, bars, or sodas. Curated recipes corresponding to each food are included in a section of the Insight app and organized by featured ingredient. For example, one of the foods delivered is farro, and there is a corresponding “Farro” section on the Insight app that provides recipes that feature farro. Each weekly package will include one food per food group, meaning one vegetable, one fruit, one grain, and one protein (which includes nuts, beans, seeds, and lentils). Foods were chosen based on fiber content (ie, ≥3 g per standard serving) and represent all food groups except for dairy given that these foods have no fiber. Secondarily, foods were selected based on ease of procurement after the intervention (eg, cost and availability). Participants will be instructed to consume the foods as part of meals and snacks and in appropriate portion sizes.

### Data Collection

#### Phase 1

Participants will complete 2 in-person data collection sessions at the University of Oklahoma Health Campus in Tulsa, one at baseline and one after the 3-month intervention (postintervention time point). Each time, they will be asked to fast for 10 hours and have a venous blood draw done, complete anthropometric assessments, and complete a measure of capillary fasting blood glucose. Venous blood samples will be collected and processed for assessment of fasting insulin. Fasting capillary blood glucose and venous insulin will be combined to calculate the Homeostatic Model Assessment of Insulin Resistance (HOMA-IR) using established calculations (fasting glucose in mmol/L × fasting insulin in μU/mL/22.5) [53,54]. If no HbA_1c_ value is on file for the previous 3 months, HbA_1c_ will be checked using an A1CNow Self Check system (PTS Diagnostics), which will be rechecked at the postintervention time point. On 2 random days after completing the baseline visit, participants will also complete 2 separate Automated Self-Administered 24-hour dietary recalls (ASA-24) to quantify fiber intake. They will also complete surveys, including a measure of basic demographic variables. Surveys will be administered in REDCap [55,56].

During the intervention period, participants will complete daily EMAs on the Insight mHealth app maintained by the University of Oklahoma Health Campus OU Health Stephenson Cancer Center mHealth Shared Resource. This will include a run-in period, where the Insight app will deliver a morning daily diary, a midmorning diary, and a midday diary. This will decrease to only a morning daily diary during the intervention period. The morning daily diary is delivered 30 minutes after waking, before typical morning mealtimes. The midmorning and midday EMAs will be delivered approximately 2 hours after normal first and second mealtimes for the day. The morning daily diary will include a checklist-type assessment of intake of high-fiber foods and static measures such as sleep, whereas all daily diaries will assess affect, food cravings, digestive symptoms, feelings of “lack of time,” motivation to eat high-fiber foods, and urge to eat tasty food. Participants will also be presented with participant-initiated questions on the app to report when a study-provided food was eaten.

To assess feasibility of the intervention, we will evaluate the following metrics according to Bowen et al [57]: implementation, demand, acceptability, and preliminary efficacy. Implementation will be assessed via review of message delivery, which will be automatically tracked on Insight. We will also track delivery of high-fiber food packages and CGM provision as defined in the protocol. For demand, we will assess participant retention in the trial as reflected by completion of data collection activities, as well as intervention uptake. Intervention uptake will be assessed via the percentage of all delivered content viewed by participants on Insight, use of CGMs by participants for the total duration requested, and participant report of consumption of provided high-fiber foods. For acceptability, we will provide acceptability surveys at the postintervention time point that include Likert-scale questions. Finally, for preliminary efficacy, we will leverage data collection on HbA_1c_ and the HOMA-IR.

#### Phase 2

After completion of the intervention and phase 1 postintervention data collection, participants will begin an observation-only period of EMA that spans 4 weeks. During this time, they will receive no intervention but complete EMAs 3 times a day as in the run-in period. EMA variables will be the same as during phase 1. Then, after completion of this period, they will repeat 2 more random, unannounced ASA-24 measures for fiber intake (“post-observation” time point).

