**Methods:**

This single-arm feasibility study includes 2 phases to preliminarily test an mHealth-based fiber intervention (phase 1) and elucidate factors that impact sustained behavior change and fiber intake after intervention end using ecological momentary assessment (EMA; phase 2). The intervention is 3 months in length and features daily EMAs with responsive text–based coping messages to target key predictors of fiber intake. EMAs will also be paired with brief (ie, <1 minute) educational videos on fiber delivered once per day. Participants will also receive weekly home-delivered high-fiber food packages and wear a continuous glucose monitor at 2 time points during the intervention as a form of biofeedback. At the baseline and postintervention time points, fasting blood glucose, hemoglobin A_1c_, and insulin resistance (Homeostatic Model Assessment of Insulin Resistance) will be assessed. After the postintervention time point, participants will continue with daily EMAs to assess factors associated with sustained fiber intake. Diet will be assessed using Automated Self-Administered 24-hour dietary recalls at the baseline and postintervention time point and after the phase 2 EMA.

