### Participants

We will recruit young adults aged 18 to 39 years who have prediabetes [48]. Classification of prediabetes is based on having a hemoglobin A_1c_ (HbA_1c_) level between 5.7% and 6.4% per American Diabetes Association guidelines [49]. Other inclusion criteria are residing in or near Tulsa, Oklahoma (where in-person data collection will take place), or nearby and being willing to travel for visits; ability to access and/or use a smartphone; and proficiency in the English language. Exclusion criteria are a suspected eating disorder based on the 26-item Eating Attitudes Test (which was reproduced with permission [50]), current use of a glucagon-like peptide-1 receptor agonist, food allergies or intolerances that preclude engagement, self-reported diagnosis of irritable bowel syndrome or inflammatory bowel disease, self-reported pregnancy or breastfeeding, or travel plans that limit intervention completion.

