### Recruitment

Participants will be recruited via community events; email distributions to students, faculty, and staff at the University of Oklahoma; directly via the medical record system of the University of Oklahoma Health Campus (MyChart); social media advertisements; provision of flyers at university health screenings; and direct communication and distribution of flyers in the clinics within internal medicine at the University of Oklahoma Health Campus in Tulsa. Prospective participants can provide documentation of an HbA_1c_ level within the prediabetes range from the previous 3 months or complete the Centers for Disease Control and Prevention Prediabetes Risk Test as part of the study screening. If prospective participants are otherwise eligible and appear to be at risk of prediabetes per the Prediabetes Risk Test, they will be invited to attend an in-person recruitment visit wherein they can complete the informed consent process, followed by a screening HbA_1c_ test. If their HbA_1c_ level is within the prediabetes range, they will be eligible for enrollment in the study. If their HbA_1c_ level is not within the prediabetes range, their participation will be considered complete, and they will be deemed ineligible.

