#### Analytic Plan

For phase 1, we will compute descriptive statistics (for all feasibility metrics) and 2-tailed paired *t* tests to examine changes in our preliminary efficacy outcomes (fiber intake, HbA_1c_, and HOMA-IR) from baseline to the postintervention time point as a measure of preliminary efficacy. For phase 2, the primary goal is to determine whether participants maintain fiber intake after the intervention and identify real-time factors that predict adherence. Adherence will be defined as maintaining fiber intake at or above 80% [59] of postintervention levels based on ASA-24 data at the start and end of the 4-week EMA period. A logistic multilevel model will be used to predict adherence (1=maintained; 0=dropped below threshold) from EMA-measured factors (eg, affect). EMA predictors will be aggregated at the participant level (eg, mean stress across the EMA period) to assess overall exposure to these factors, whereas daily fluctuations will be modeled using within-person deviations from each participant’s mean. To assess how the influence of these predictors changes over time, we will use time-varying effect modeling, allowing for the examination of whether certain factors (eg, stress) exert stronger effects on adherence early vs late in the observation period. Additionally, we will explore the role of EMA variability, calculating within-person fluctuations (eg, SD of stress) to test whether greater instability in these factors predicts lower adherence. We will assess patterns of missing data and conduct sensitivity analyses assuming different missing data mechanisms. For example, we will consider a multiple imputation approach, which uses baseline characteristics to account for potential missing at random mechanisms [60,61].

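### The HbA1c value that admits a participant can also serve as the baseline of the paired t test, so regression to the mean and, for chart values, assay and timing differences can mix with any effect

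*Protocol article*

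**What the plan says.** - **Entry criterion** (Participants): "Classification of prediabetes is based on having a hemoglobin A_1c_ (HbA_1c_) level between 5.7% and 6.4"%.
- **Two routes in** (Recruitment): "Prospective participants can provide documentation of an HbA_1c_ level within the prediabetes range from the previous 3 months". Otherwise, those who appear at risk on a questionnaire take a study HbA1c test after consent: "If their HbA_1c_ level is within the prediabetes range, they will be eligible for enrollment in the study".
- **Baseline measurement** (Data Collection, Phase 1): "If no HbA_1c_ value is on file for the previous 3 months, HbA_1c_ will be checked using an A1CNow Self Check system", followed by "which will be rechecked at the postintervention time point". No assay is given for a documented value, and no further HbA1c reading between qualification and the start of the intervention is described.
- **Abstract, Methods**: "At the baseline and postintervention time points, fasting blood glucose, hemoglobin A_1c_, and insulin resistance (Homeostatic Model Assessment of Insulin Resistance) will be assessed". No exception is made for participants with a value on file.
- **Analysis** (Analytic Plan): "2-tailed paired *t* tests to examine changes in our preliminary efficacy outcomes". HbA1c is one of the three outcomes listed, with fiber intake and HOMA-IR.
- **Design** (Study Design; Power): single arm, up to 80 participants, 64 expected to complete postintervention data collection, and a phase 1 minimum of 30.

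**The concern.** A reading that must fall inside a window to admit someone is partly selected for its error. If the people tested centre below the middle of the window, admitted readings are too high on average and fall on retest with no intervention at all. In a single-arm study nothing subtracts that fall.

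A second problem affects participants who enter on a chart value. Their baseline may come from another assay and be up to 3 months old when accepted, while the only study device named is the A1CNow system. Their change then includes any between-assay bias and any drift before the intervention began.

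At stake is a P value for one of the preliminary efficacy outcomes. The measurement rule creates the problem, and no later analysis can recover a baseline that was never taken.

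**Working it through.** **The plan's own figures.** The protocol gives no power or precision figure for HbA1c. Its one power statement concerns phase 2 and does not bear on this point. The n used here is 80 × 0.80 = 64. Alpha is not stated; two-sided 0.05 is assumed.

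**Assumed inputs (none is in the protocol).** True HbA1c in the people tested is normal with mean μ from 5.4 to 6.05 and SD σb of 0.30 to 0.35. The error SD of a single reading, σe, is 0.10 to 0.30. True values do not change. The window is 5.7 to 6.4.

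**Formulas.**
- Observed SD: s = √(σb² + σe²). Reliability: r = σb²/s².
- Mean of admitted readings: m = μ + s[φ(A) − φ(B)]/[Φ(B) − Φ(A)], with A = (5.7 − μ)/s and B = (6.4 − μ)/s.
- Expected change with no effect: d = (1 − r)(μ − m).
- Variance of change: σb²(1 − r) + σe² + (1 − r)² × Var(admitted readings).
- Chance of P < 0.05: noncentral t with n − 1 df and noncentrality d√n/SD of change.

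**One case in full** (μ = 5.6, σb = 0.35, σe = 0.15).
- s = √(0.1225 + 0.0225) = 0.381; r = 0.1225/0.145 = 0.845.
- A = 0.263, B = 2.10, so m = 5.943.
- d = 0.155 × (5.6 − 5.943) = −0.053.
- SD of change = √(0.0190 + 0.0225 + 0.0008) = 0.206.
- Noncentrality = −0.053 × 8/0.206 ≈ −2.07. The test is significant in 53% of trials with no effect.

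**Full range over σb and σe.**

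| Source mean | Change with no effect | P<0.05, n=64 | P<0.05, n=30 |
|---|---|---|---|
| 5.4 | −0.037 to −0.263 | 56% to >99% | 30% to 96% |
| 5.6 | −0.025 to −0.180 | 30% to 96% | 16% to 71% |
| 5.8 | −0.014 to −0.099 | 12% to 54% | 8% to 28% |
| 5.9 | −0.008 to −0.060 | 8% to 24% | 6% to 13% |
| 6.05 (window centre) | 0 | 5% | 5% |

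**Sensitivity.**
- If true HbA1c also varies over 3 months, so that the SD of change is 0.3, the worked case falls from 53% to 29% (0.053 × 8/0.3 = 1.42).
- If only chart-value participants carry their qualifying value as baseline and they are half the sample, the expected change in the worked case halves: 0.5 × −0.053 = −0.027.

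**Assay difference.** Mean shift = share with a chart baseline × between-assay bias. With assumed shares of 25% to 75% and biases of 0.1 to 0.3 points, the shift is 0.25 × 0.1 = 0.025 to 0.75 × 0.3 = 0.225 points, in either direction. For scale, n=64 gives 80% power for a standardised change of 0.356, which is 0.107 points at an SD of change of 0.3.

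**The case against.** Feasibility is the primary outcome, the sample size does not rest on HbA1c, and no progression rule uses its P value. Limitations already says that a single arm cannot fully establish effects and calls for randomized trials. All of this stands and lowers the severity. It does not remove the point: the caveat is general and names neither regression to the mean nor assay mismatch, and this bias, unlike the missing control arm, can be avoided within the design.

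Four stronger readings are tempting, and the protocol does not support them:

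- **A significant fall is likely even with no effect.** This depends wholly on the assumed source mean and error. The table runs from 5% to nearly 100%.
- **Most people tested lie below the window.** The Introduction's one in 4 with prediabetes describes young adults in general. The pool tested here is enriched by a risk questionnaire or by documented prediabetes, and its mean is not given.
- **For every participant, one reading both selects and serves as baseline.** This is an inference from joining Recruitment and Data Collection. If a value on file means only outside documentation, screening-route participants would get a separate A1CNow check at baseline.
- **Chart-value participants have no postintervention HbA1c.** The recheck clause can be parsed that way, but the Abstract plans HbA1c at both time points and the Analytic Plan a paired test. The wording is loose; it does not show that the value is missing.

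**Conclusion.** The point holds at moderate severity. The protocol allows a qualifying HbA1c, of unspecified assay and up to 3 months old on the documentation route, to serve as the baseline of a single-arm paired test. It appears to allow the same for the screening value. The mechanism is certain; its size is not. Under assumed true SD of 0.30 to 0.35 and reading-error SD of 0.10 to 0.30, the change with no effect lies between about −0.26 points and 0, and the false-positive rate at n=64 between nearly 100% and 5%. Both are governed mainly by how far the mean of those tested lies below 6.05. Rates are lower at n=30, or if true HbA1c also varies over the 3 months. The assay component has unknown sign and could hide an effect as easily as create one. The direct selection argument does not extend to fiber intake or HOMA-IR, which are not entry criteria.

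**What to change.** 1. Reconcile the Abstract with Data Collection: state whether every participant has HbA1c measured at both visits, and whether a value on file includes the study's own screening result.
2. Use the chart or screening HbA1c for eligibility only.
3. Measure HbA1c in every participant by the same method at the baseline and postintervention visits, and run the paired analysis on those two values only. This removes the expected selection and assay artefacts. Other single-arm threats remain.
4. Where no separate baseline reading exists, report the change descriptively with a confidence interval and no P value, and name regression to the mean as a limitation.

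**Cost:** up to about 80 baseline tests, plus postintervention tests for any chart-value participants not already due a recheck, and changes of wording. Blood is already taken at both visits. Results gives April 2026 as the planned start of enrollment; the change is needed before baseline visits begin, because a missed baseline reading cannot be collected later.

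### The baseline fiber recalls come after the visit at which the first CGM is given, and no rule keeps them ahead of intervention exposure

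*Protocol article*

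**What the plan says.** In the protocol article, Data Collection (Phase 1) times the baseline recalls thus: "On 2 random days after completing the baseline visit, participants will also complete 2 separate Automated Self-Administered 24-hour dietary recalls". It gives no window and no order relative to any intervention component.

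Biofeedback times the first sensor: "Participants will be given a G7 device at their baseline visit and walked through how to self-insert it". Only the second device carries a later instruction, namely self-insertion at about 6 weeks. The same section says that the CGM is not a measure of glycemic control but "will be used as a form of biofeedback to allow participants to observe the glycemic effects of adding high-fiber foods to their diet".

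The Overview of the intervention states that "GO-FAR includes 3 core elements", and two of these are "biofeedback in the form of CGMs, and home-delivered high-fiber foods". The Abstract has participants "wear a continuous glucose monitor at 2 time points during the intervention as a form of biofeedback".

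On the diaries, Data Collection says: "This will include a run-in period, where the Insight app will deliver a morning daily diary, a midmorning diary, and a midday diary". The morning diary includes a checklist of high-fiber foods, and all diaries ask about motivation to eat such foods.

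The Analytic Plan compares fiber intake, HbA1c and HOMA-IR between baseline and postintervention with two-tailed paired t tests.

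**The concern.** A before-and-after comparison needs a before value taken ahead of the intervention. Here one active component is placed in participants' hands at the visit, and the diet measure that serves as the before value follows on unspecified later days. Participants may by then be watching their glucose, answering diary questions about fiber, or both.

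The trial has one arm, so no control group would cancel a shift in the starting value. Fiber intake is the direct dietary target of the intervention, and its estimated change would naturally inform the randomized trials that the Limitations section calls for. A starting value recorded under exposure cannot be repaired afterwards.

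**Working it through.** **1. Order of events, section by section**

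| Event | Timing given | Section |
|---|---|---|
| First CGM given, insertion taught | At the baseline visit | Biofeedback |
| Fasting blood draw and capillary glucose | At the baseline visit | Data Collection, Phase 1 |
| HbA1c | On file from the previous 3 months, or checked | Data Collection, Phase 1 |
| Two baseline recalls | Random days after the visit, no window | Data Collection, Phase 1 |
| Run-in, three diaries a day | Length not given | Data Collection, Phase 1 |
| Videos and weekly foods | Start day relative to the recalls not given | Intervention |

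The recalls are the only one of these baseline efficacy measures placed after the CGM is handed over. The run-in does not settle the matter. Data Collection introduces it as part of the intervention period, then says that the diaries decrease to one a day during the intervention period. The run-in is thus inside that period in one sentence and ahead of it in the next.

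**2. Effect of a shifted starting value**

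Let D be the true mean change in fiber and c the mean shift already present at the baseline recalls.

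Expected estimated change = D − c. Share of the true change hidden = c / D.

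A positive c (fiber already raised) understates the gain. A negative c (fiber lowered) overstates it.

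**3. Illustration**

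The document gives no effect size, SD or power for the fiber change, so there is no stated figure to reproduce. The only power statement concerns phase 2 and does not depend on this point.

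The one input from the document is n = 64 completers (80 × 0.80). Assumed: two-sided alpha 0.05; D = 4 or 8 g/day; SD of change 8 or 12 g/day; c = 0 to 3 g/day. Power is for a paired t test, from the noncentral t distribution with noncentrality (D − c)/SD × √64.

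| D | SD | c = 0 | c = 1 | c = 2 | c = 3 |
|---|---|---|---|---|---|
| 4 | 8 | 0.98 | 0.84 | 0.50 | 0.17 |
| 4 | 12 | 0.75 | 0.50 | 0.26 | 0.10 |
| 8 | 12 | 1.00 | 1.00 | 0.98 | 0.91 |

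Share hidden for c = 1 to 3: 1/4 to 3/4 (25% to 75%) when D = 4, and 1/8 to 3/8 (about 13% to 38%) when D = 8.

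The same arithmetic works in reverse. With no true change and c = −2, the expected estimate is 0 − (−2) = +2 g/day, and at SD 8 the test would reject with probability 0.50.

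The effect therefore runs from negligible to large, depending on values that the document does not supply.

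**The case against.** The strongest reply is that the text shows only a possibility. The device is given and insertion is walked through, but no start of wear is tied to the recall days; the Abstract places wear during the intervention; and the recalls might fall in a run-in before videos and foods. This stands. A reader might infer that the baseline value is contaminated and the change biased, but the document establishes only that nothing prevents it.

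The direction is also open. The Introduction says that people may fear fiber-containing foods because they are carbohydrates, and the Discussion says that starch in foods such as beans can raise glucose acutely. A participant watching a sensor before the later videos explain this might eat less fiber. Understatement is the likelier direction given the CGM's stated purpose, but it is not certain.

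A reader might further infer that the postintervention recalls fall after support has ended, since adherence is judged "based on ASA-24 data at the start and end of the 4-week EMA period" and the baseline recalls follow their visit. The document does not support that. Data Collection (Phase 2) starts the observation period only once the intervention and phase 1 postintervention data collection are complete, and recalls at the start of the EMA period are compatible with this.

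It can also be said that recall windows are detail for a full protocol, and that the study schematic, not available here, may show the sequence. That would excuse a missing window. It does not remove the stated order, which puts the recalls after the visit at which a core component is handed over.

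Finally, recalls taken before the first diary would count any reaction to the diaries as part of the change. That is a fair reason to make the diary part of the rule a preference only.

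**Conclusion.** The point holds as a weakness in the order of measurement. The fiber starting value may be taken under intervention exposure, and no rule prevents this. If the CGM works as intended, the fiber change is understated by the amount of the early rise. That amount cannot be derived from the document: the 1 to 3 g/day used above is an assumption with no anchor in it, as are the true gains and SDs.

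The reach is narrow. The primary outcome is feasibility, and the preliminary efficacy data named under Data Collection are HbA1c and HOMA-IR; fiber joins them only in the Analytic Plan. Baseline HOMA-IR uses samples taken at the visit itself. The phase 2 adherence threshold is set from postintervention fiber levels, so the baseline recalls do not enter it. What is at risk is the preliminary estimate of change in fiber intake. The change is worth making because it is cheap and because that estimate concerns the intervention's direct target.

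**What to change.** State in Data Collection (Phase 1) that both baseline recalls are completed after consent but before the first sensor is worn and before the first video or food package, and preferably before the first diary prompt. One way is to teach insertion at the baseline visit, as now planned, and have participants start the sensor once both recalls are done. State also whether the run-in lies before or within the intervention period, and how long it lasts.

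Record each recall date relative to first sensor wear, and repeat the fiber analysis without any recall taken later.

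The cost is a few days' delay to start-up and a first sensor inserted away from the visit, as is already planned for the second. No new procedure or extra visit is needed if insertion is still taught at the baseline visit. The repeat analysis will rest on fewer recalls, and on fewer participants if both of a person's recalls were late.
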